## 16.2 Level of significance and power

All tests will be conducted with an error of 1st kind  $\alpha = 5\%$ , two-sided.

Tests of secondary variables will be carried out in the area of exploratory data analysis. Therefore, corresponding p-values are to be regarded as exploratory ones and no adjustments for multiple testing will be made.

Sample size calculations are to be performed with a power of 80%

## 16.3 Statistical hypotheses

The primary objective is the efficacy of target controlled fluid therapy with a hyperoncotic compared to an iso-oncotic balanced HES 130/0.42 solution, so that the following hypotheses need to be tested

for the first primary variable (amount of HES-solution [VR]):

$H_{01}$  (null hypothesis):

VR [hyperoncotic HES-solution] = VR [iso-oncotic HES-solution]

$H_{A1}$  (alternative hypothesis, two-sided):

VR [hyperoncotic HES-solution]  $\neq$  VR [iso-oncotic HES-solution]

and for the second primary variable (days until fully on oral diet [DD]):

$H_{02}$  (null hypothesis):

DD [hyperoncotic HES-solution] = DD [iso-oncotic HES-solution]

$H_{A2}$  (alternative hypothesis, two-sided):

DD [hyperoncotic HES-solution]  $\neq$  DD [iso-oncotic HES-solution]

## 16.4 Sample Size

The first primary variable, i. e. amount of plasma volume replacement therapy (in addition to a basal electrolyte infusion), will serve to calculate sample size. It is assumed that 250ml difference between the two HES treatment arms is clinically relevant.

It is roughly calculated that 228 patients shall be included which is based on the following assumptions: 69 patients per group, supposing an effect size (difference of means/(common standard deviation) =  $\frac{1}{2} = 0.5$ , error of the 1st kind  $\alpha = 5\%$  (two-sided), Power = 80% and the nonparametric Mann-Whitney U-Test (Calculations with

nQuery Advisor, version 6.0). Taking the drop-out rate of 10% into consideration, a sample size of 76 patients per group will be needed.

However, at present no reliable information is available on the amount of plasma volume requirement in elective pancreatic surgery. Thus, an internal pilot phase including 60 patients (including drop-outs) will be performed in order to re-calculate total sample size. For re-calculation the pooled variance will be assessed on the grounds of clinical relevant difference without unblinding. Type I error for both phases of the study will strictly be maintained. (Kieser and Friede, 2000 and 2003)

For the second primary endpoint it is assumed that 1.5 day difference between the two treatment arms will be achieved. Based on hospital's own data an effect size (difference of means/ common standard deviation) of 0.698 is calculated which reveals that inclusion of 69 patients – as for the first primary endpoint (without dropouts) – will lead to a power of 97%. A sample size of only 37 (per group) is demanded to achieve a power of 80%. Therefore, enough power is ensured to prove the second primary endpoint after significance of the first. After pilot phase, the re-estimation of the (pooled) variance will also be accomplished for the second primary variable in order to ensure a sufficient power comparing the two treatments with the former re-calculated sample size (see above).

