| Number of Sites & Countries | multicentric, Germany                                                                                                                                                                                                                                                                                                                                                                                                                                                                                                                                                                                                                                                                                                                                                                                                           |
| Sample Size                 | 
Estimated: 228. The study will be performed in 2 phases:
 
The study will begin with an internal pilot phase including 60 patients. At the end of this pilot phase, the pooled variance with respect to the primary variables will be estimated without unblinding and will be used for confirmation respectively recalculation of the initially estimated sample size. Interim analysis will also serve for deciding of premature termination of the study for futility.
 
For the comparison of the defined groups at end of study, the error of the 1st kind <math>\alpha</math> will be strictly adhered to with this procedure (Kieser et al., 2000 and 2003).
                                                                                                                          |

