This sample size also should be sufficient for the 2nd primary variable (for details see section 16)

Estimated total sample size:

Internal pilot phase

[figure not shown]

The study will be performed in three study centres in Berlin and Bonn, Germany.

\*\* may change according to calculation of pooled variance after internal pilot phase.

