### **16.7 Criteria for the termination of the study**

If after pilotphase (after 60 patients) the calculation of the pooled variance reveals that the estimated total number of 228 patients will be exceeded the study will not be carried on but stopped for futility after the pilot phase.

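### Because any increase above 228 stops the trial and no minimum is set, the re-estimation can only confirm or reduce N; at the planning SD of 500 mL, power given continuation is about 70–76%, not 80%

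*Protocol*

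**What the plan says.** The fixed planning figures are in Protocol 16.2 and 16.4. Section 16.2 states "Sample size calculations are to be performed with a power of 80"%, with two-sided 5% tests. Section 16.4 adds: "It is assumed that 250ml difference between the two HES treatment arms is clinically relevant". It reaches 69 per group for the Mann-Whitney test, "supposing an effect size (difference of means/(common standard deviation") of 0.5, then 76 per group with drop-outs and 228 over three arms. It also concedes that no reliable information exists on volume requirement in this surgery.

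For that reason "an internal pilot phase including 60 patients (including drop-outs) will be performed in order to re-calculate total sample size", using a pooled variance obtained without unblinding. The synopsis says the estimate "will be used for confirmation respectively recalculation of the initially estimated sample size". A note under the sample size diagram in section 8 says the number "may change according to calculation of pooled variance after internal pilot phase". Section 16.4 later speaks of the second endpoint's power at the re-calculated size, so the recalculated N is the one carried forward.

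Section 16.7, like 9.4.1, covers the upward case. If the pooled variance shows that "the estimated total number of 228 patients will be exceeded the study will not be carried on", the trial is stopped for futility after the pilot phase. No section covers the downward case.

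**The concern.** An internal pilot protects power because N grows when the variance turns out larger than planned. Here that branch ends the trial, and only the branch that keeps or shrinks N is left.

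The trials that continue are those whose pilot SD came out at or below the planning value. If the true SD is 500 mL, many of them continue because the pilot SD was low by chance. Cutting N to match that estimate leaves too few patients.

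At stake is the first endpoint, amount of HES, which is the gate: time to full oral diet is tested confirmatorily only if the first endpoint is significant. The 80% for the first endpoint and the 97% for the second are both stated at 69 per group, a number that a continuing trial need not reach.

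**Working it through.** **Inputs.** Alpha 5% two-sided and power 80% (16.2). Difference 250 mL, effect size 0.5, 69 evaluable and 76 randomised per group (16.4). Pilot of 20 per arm including drop-outs (section 8), so about 18 evaluable after 10% loss. The SD is not stated; it follows as 250/0.5 = 500 mL.

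**Reproducing the plan's figure.** Noether's formula for the Mann-Whitney test is n = (z₀.₉₇₅ + z₀.₈₀)² / [6(p − 0.5)²], with p = Φ(d/√2).
- At d = 0.5, p = 0.638 and n = 7.849 / (6 × 0.1382²) = 68.5, so 69 per group. Power at 69 is 80.3%.
- 69 × 1.1 = 75.9, so 76; 3 × 76 = 228. The plan's number is reproduced.

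**Where the stop falls.** Setting n = 69 and solving gives d = 0.498, an SD of about 502 mL. A pilot SD above that stops the trial; one below it permits a smaller N.

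**Simulation at true SD 500 mL, difference 250 mL.** Normal data, 18 evaluable per arm in the pilot, n recalculated by Noether, stop if n > 69, otherwise continue to the recalculated n and apply a two-sided 5% Mann-Whitney test; 20,000 runs each. The protocol does not say how the blinded variance is formed, so several forms were tried. In the first row the crystalloid mean lies midway between the HES arms.

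| Variance estimate | Continues | Power given continuation | Mean n per arm | Continues and rejects |
|---|---|---|---|---|
| One-sample, three arms | 46% | 73.7% | 60.4 | 34% |
| One-sample, two HES arms | 44% | 71.1% | 58.7 | 32% |
| Same, adjusted for the assumed difference | 54% | 70.5% | 56.8 | 38% |
| Within-group, three arms | 55% | 76.3% | 59.4 | 42% |
| Within-group, two arms | 54% | 74.7% | 57.4 | 40% |

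With no pilot drop-out, power given continuation is 73.5–76.4%. If the crystalloid mean lies 500 or 750 mL above the lower HES arm and enters a one-sample variance, continuation falls to about 24% or 6%, with power given continuation still about 74%.

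**Separating the two causes at 500 mL.**
- Stop rule kept, N held at 69 evaluable per arm: 79.4–82.1% given continuation; about 77–84% over all repeat runs and estimators.
- Re-estimation in both directions, no stop: about 78–81%.
- Stop and cut together: about 70–76% (68–78% over repeat runs).

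**Other true SDs** (three of the estimators, 8,000 runs each; the last column is Noether power at a fixed 69 per arm):

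| True SD | Continues | Power given continuation | Mean n per arm | Fixed 69 |
|---|---|---|---|---|
| 400 mL | 98–100% | 79–82% | 45–48 | 93% |
| 450 mL | 83–89% | 75–80% | 52–56 | 87% |
| 550 mL | 15–27% | 64–72% | 59–63 | 73% |

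A repeat run gave 63–71% at 550 mL. There, part of the shortfall comes from the larger SD itself: even a fixed 69 would not reach 80%.

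**Second endpoint.** At its stated effect size of 0.698 the same formula gives 80% at 37 per group and 97% at 69, matching 16.4. At 57–60 per group it gives 94–95%, and at 41 (about the 5th percentile of the reduced sizes) 84%.

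**The case against.** **The figure is one point on a curve.** This stands. The protocol calls its calculation rough and never states an SD of 500 mL. A reader might infer that power is 70–76% whatever happens. If the SD is clearly smaller, the reduction works as intended and holds about 80%.

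**The protocol does not promise 80% conditional on passing the stop.** Also fair: 80% is a planning input. But it is the only power given for the first endpoint, with nothing said about what the stop-or-cut rule does to it. The unconditional chance of continuing and rejecting is lower still, about 32–42% in the first table.

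**The cut is inferred.** No sentence says enrolment will drop below 228, and the section 8 note belongs to a diagram not available here. If 228 was always meant as a minimum, there is no material shortfall at 500 mL. Still, 16.4 carries the recalculated size forward and nothing excludes a reduction, so the cut is the natural reading. The point cannot simply wait for the statistical analysis plan: section 16.1 requires that plan only before database closure, while N is decided after 60 patients.

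**Downward re-estimation is not a flaw in itself.** A reader might infer that it is. The check without the stop, at about 78–81%, shows otherwise.

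**The second endpoint is protected.** Largely true. A reader might infer that it is underpowered in its own right, but at its stated effect size its power stays above 80% at most of these sizes, and 16.4 plans to re-check its variance after the pilot. What it loses is mainly the chance to be tested.

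Nothing here shows an effect on the type I error.

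**Conclusion.** The concern holds in a conditional form. Under the text as written, a continuing trial can only confirm or reduce N. If the planning assumption is exactly right, power for the gatekeeping endpoint given continuation falls about 4 to 10 percentage points short of 80%. The shortfall appears under every variance estimator tried at that SD.

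The conclusion assumes that N is actually cut to the recalculated value, that the data are roughly normal, and that the true SD is near 500 mL. It largely vanishes around 400 mL.

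**What to change.** Preferred: state in 16.4, and in matching words in the synopsis and section 8, that a trial continuing after the pilot phase will not go below the planned 76 per arm (228 in total). This needs no patients beyond those already planned. It does turn the re-estimation into a continue-or-stop check and gives up the smaller trial if the SD is clearly below 500 mL. At 400 mL, for example, about 21–24 more evaluable patients per arm would be enrolled than the recalculation asks for (69 against 45–48).

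Alternative: keep the reduction and say so explicitly. Replace the unconditional 80% by the simulated power of the whole procedure, stop included, over a range of true SDs such as 400–550 mL, naming the blinded variance estimator used. Qualify the 97% for the second endpoint in the same way. This costs a short simulation and a few lines of text.

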| Title of Study              | PROSPECTIVE, CONTROLLED, DOUBLE-BLIND, RANDOMIZED MULTICENTRIC STUDY ON THE EFFICACY AND SAFETY OF TARGET CONTROLLED VOLUME REPLACEMENT THERAPY WITH A HYPERONCOTIC BALANCED HES 130/0.42 SOLUTION VS AN ISOONCOTIC BALANCED HES 130/0.42 SOLUTION COMPARED TO A BALANCED ELECTROLYTE SOLUTION IN ELECTIVE SURGERY OF THE PANCREATIC HEAD                                                                                                                                                                                                                                                                                                                                                                                                                                                                                       |
| Investigational Products    | 
Investigational Test Product:
 
Tetraspan 10% (hyper-oncotic balanced HES 130/0.42 solution)
 
Investigational Reference Product:
 
Tetraspan® 6% (iso-oncotic balanced HES 130/0.42 solution)
 
Descriptive control:
 
Sterofundin ISO (balanced electrolyte solution)
 
A treatment group receiving solely a crystalloid/electrolyte volume replacement is included in the study as in various hospitals and countries respectively this treatment is still a standard in surgery including pancreatic surgery. As crystalloid solutions, however, display another volume effect*, than colloidal solutions (*thus leading to a distinct higher requirement of volume which could be easily recognised even when blinded) this treatment group will only serve as a descriptive control.
 |

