## **8 STUDY DESIGN**

This is a prospective, randomized, controlled, double-blind, multi-centre phase IV study performed in three parallel groups.

Comparison will be made of a hyper-oncotic (10%) balanced HES 130/0.42 solution with an iso-oncotic (6%) balanced HES 130/0.42 solution on the basis of a multiple endpoint. The principle of ordered hypothesis will be used [see section 16 statistics]

for testing the two primary endpoints: “the intra-operative amount of colloidal volume replacement therapy during target directed volume replacement therapy” (first), subsequently “days until fully on oral solid diet” (second).

A third treatment arm (as a descriptive control) will comprise the administration of solely a balanced crystalloid fluid replacement. This group is included in the study as in various hospitals and countries respectively volume replacement solely with electrolytes is still a standard in surgery including pancreatic surgery. As crystalloid solutions, however, display another volume effect\* than colloidal solutions (\*thus leading to to a distinct higher requirement of volume which could be easily recognised even when blinded) this treatment group will only serve as a descriptive control.

The study will be started with an internal pilot phase which serves for recalculation of sample size for the first primary variable respectively for ensuring sufficient power for the second primary variable. Interim analysis will also serve for deciding of premature termination of the study for futility. This interim analysis will be performed by estimating the pooled variances for both primary endpoints without unblinding [see section 16 statistics].

In the first phase of the study (internal pilot phase) the number of patients is 20 (including drop-outs) for each treatment arm.

Beside this two-phase design with a number of 60 patients in the pilot phase, a rough estimation of the sample size (for the 1st primary variable) to expect resulted in:

69 patients per group, supposing an effect size (difference of means)/(common standard deviation) =  $\frac{1}{2} = 0.5$ , error of the 1st kind  $\alpha = 5\%$  (two-sided), Power = 80% and the nonparametric Mann-Whitney U-Test (Calculations with nQuery Advisor, version 6.0). Taking a drop-out rate of 10% into consideration, a sample size of 76 patients per group will be needed.

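### The blinded pilot variance does not say how the crystalloid arm is handled; taken over all three arms it is biased upward and pushes the trial towards a false futility stop

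*Protocol*

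**What the plan says.** - **Blinded variance.** The synopsis (Section 3, Sample Size) says that "the pooled variance with respect to the primary variables will be estimated without unblinding". Section 8 says "This interim analysis will be performed by estimating the pooled variances for both primary endpoints without unblinding". Section 16.4 says "For re-calculation the pooled variance will be assessed on the grounds of clinical relevant difference without unblinding". Section 16.6 repeats that only a pooled variance is estimated, without unblinding.
- **Who is in the pilot.** Section 8 sets 20 patients for each of the three arms, 60 in all.
- **What is compared.** Section 16.3 tests HES 10% against HES 6% only. The crystalloid arm is a descriptive control. The only difference stated for the first primary variable concerns the HES arms: "It is assumed that 250ml difference between the two HES treatment arms is clinically relevant" (Section 16.4).
- **What is expected of crystalloid.** The synopsis describes the crystalloid volume effect as "leading to a distinct higher requirement of volume which could be easily recognised even when blinded"; Section 8 says the same. Neither gives a figure in ml.
- **What the variable is.** Section 12.1 and the synopsis define the first primary endpoint as ml of HES. Section 16.4 bases the sample size on the amount of plasma volume replacement given on top of the basal infusion, which is not restricted to HES.
- **What blinded records show.** Under Section 9.5 every arm receives the same number of sequentially numbered bottles for a given body weight. The crystalloid arm gets no HES. The HES 10% arm moves to blinded crystalloid at its daily maximum; in the 70 kg example, bottles 1–4 are HES 10% and bottles 5–7 crystalloid.
- **What the result decides.** Under Sections 9.4.1 and 16.7, a recalculated total above 228 does not enlarge the trial. It stops it for futility after the pilot.

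**The concern.** The variance needed is that of the first primary variable within the two HES arms. Blinded records offer two routes, and neither delivers it.

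For ml of HES, a bottle number does not reveal its content, so the quantity is unavailable without the code. For total add-on volume, the quantity is available. But a variance over all 60 patients then contains the differences between three arm means, including the crystalloid shift that the protocol itself predicts. Subtracting a term for the 250 ml HES difference, which is one reading of the Section 16.4 sentence, leaves that shift in place. No HES–crystalloid difference is stated that could be subtracted instead.

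At stake is the continuation of the trial. Because a total above 228 means stopping, an upward bias becomes a false futility stop, driven by an arm that appears in no confirmatory hypothesis.

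**Working it through.** **Inputs from the protocol.** Two-sided alpha 5% (Section 16.2); "Power = 80% and the nonparametric Mann-Whitney U-Test", effect size 0.5, relevant difference 250 ml, 10% drop-out (Section 16.4); 1:1:1 allocation (Section 9.5); 20 per arm in the pilot (Section 8). A difference of 250 ml at effect size 0.5 implies a within-arm SD of 250/0.5 = 500 ml.

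**The plan's own figure.** Noether's formula for the Mann-Whitney test is n per group = (z₀.₉₇₅ + z₀.₈₀)² / [6(p − 0.5)²], with p = Φ(d/√2).
- d = 0.5 gives p = 0.6382 and n = 7.849/[6 × 0.1382²] = 68.5, so 69.
- 69 × 1.1 = 75.9, so 76 per group; 76 × 3 = 228. The stated 69, 76 and 228 reproduce.
- With the same steps, the total passes 228 once the estimated SD exceeds about 502 ml. The limit therefore sits almost exactly on the planning assumption.

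**Assumptions not in the protocol.** Normal data; equal within-arm SD; HES 10% needs 250 ml less than HES 6%; crystalloid needs D ml more than HES 6%, with D = 250, 500 or 1000.

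**Variance over all 60 patients.** Relative to HES 6%, the arm means are −250, 0 and D. Let b be the variance of these three means (divisor 3). The expected one-sample variance is σ² + (60/59)b. With σ = 500:

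| D (ml) | b (ml²) | Expected variance (ml²) | SD (ml) | n per group | × 1.1 | Total N |
|---|---|---|---|---|---|---|
| 250 | 41,667 | 292,373 | 541 | 80 | 88 | 264 |
| 500 | 97,222 | 348,870 | 591 | 95 | 105 | 315 |
| 1000 | 291,667 | 546,610 | 739 | 147 | 162 | 486 |

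**Subtracting the HES term.** The planned HES contribution is 250²/4 = 15,625 ml². Removing it leaves 276,748, 333,245 and 530,985 ml², so SDs of 526, 577 and 729 ml. The n per group is 76, 91 and 143, or 84, 101 and 158 with drop-out, and the totals are 252, 303 and 474. Most of the inflation remains.

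**Chance that a pilot gives a total above 228** (simulated, 20 per arm, normal data, true SD 500 ml):

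| Estimator | D = 250 | D = 500 | D = 1000 |
|---|---|---|---|
| Three arms, uncorrected | 77% | 95% | about 100% |
| Three arms, minus 15,625 | 66–67% | 92% | about 100% |
| HES arms only | about 46% | about 46% | about 46% |

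**A case away from the limit.** With a true SD of 400 ml, d = 250/400 = 0.625. This gives 45 per group, 45 × 1.1 = 49.5, so 50, and 150 in total. The trial is comfortably feasible. A HES-only variance exceeds 228 in about 2% of pilots. The uncorrected three-arm variance does so in about 9–10%, 54% and nearly 100% for D = 250, 500 and 1000 ml. Here the effect is almost entirely bias.

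**The case against.** - **Lumping is not stated.** A reader might infer that the protocol plans a one-sample variance over all 60 patients. It does not say so: it says pooled and without unblinding, frames 250 ml as a difference between the HES arms, speaks of two treatments for the second endpoint, and cites a paper on blinded re-estimation in multi-arm trials. This stands: the handling of the crystalloid arm is unspecified. But followed as written, with no unblinding and no stated crystalloid difference, the text leaves no unbiased route.
- **The variance can be computed.** A reader might also infer that no blinded variance exists. That holds for ml of HES only. Add-on volume can be totalled blind, and the independent statistician who keeps the list (Section 9.5) could compute a within-arm variance. The protocol does not assign that task.
- **The size is assumed.** This stands. No crystalloid excess in ml is given; only the direction is documented.
- **Chance does much of the work at SD 500.** This stands too. The 77%, 95% and near 100% must be read against 46%, which comes from placing the limit at the planning value. After subtracting the HES term, the low-end excess is about 21 points and 24 patients (252 − 228). The SD 400 case separates bias from this knife-edge.
- **Crystalloid patients entered as 0 ml of HES.** One might quantify that case as well. It requires the code, which is exactly what is withheld, and the result depends on HES means that the protocol does not give. It is not relied on.
- **The analysis plan may settle it.** Section 16.1 requires that plan only before database close, which may come after the pilot decision. The blinded rule, the three-arm pilot and the 228 limit are fixed in the protocol itself.

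**Conclusion.** The point holds in this form: the protocol does not say how the crystalloid arm is treated in the blinded variance, and it names the first primary variable in two ways. One version cannot be derived blind; the other, taken over all three arms, is biased upward. The 250 ml term does not remove the bias.

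The direction follows from the protocol's own expectation about crystalloid. The size rests on normal data, equal SDs and an assumed crystalloid excess. Over 250 to 1000 ml, the excess in total N is 36 to 258 patients uncorrected (264 − 228 and 486 − 228). At SD 500 ml, the excess chance of stopping over a correct estimate runs from about 20 points to more than 50. This needs correcting before the pilot look, because the result decides whether the trial continues.

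**What to change.** In Sections 8, 16.4 and 16.6, with matching text in the synopsis:

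1. Name one variable for re-estimation, and reconcile the add-on volume of Section 16.4 with the ml of HES in Section 12.1 and the synopsis. Excluding the crystalloid arm does not settle this, since add-on volume in the HES 10% arm can include blinded crystalloid.
2. State that the independent statistician who already holds the list computes the pooled within-arm variance from the two HES arms only, and releases only the resulting SD to the otherwise blinded team. An alternative is the one-sample variance of the two HES arms combined, minus 250²/4. If the arms differ by 250 ml, this recovers √(250,000 + (40/39) × 15,625 − 15,625) ≈ 500 ml. If they do not differ, it gives about √(250,000 − 15,625) = 484 ml, so the within-arm version is safer.
3. Base the 228 decision in Sections 9.4.1 and 16.7 on that estimate.
4. Use the same HES-arms-only estimate for days to oral diet. This is for consistency; no bias was calculated for that endpoint.

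The cost is wording and one restricted calculation. The downside is small: one person outside the trial team, who already holds the list, uses the code at the pilot look. The roughly 46% chance of exceeding 228 at a true SD of 500 ml would remain; it belongs to the stopping rule, not to this point.
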